##### Processing and analysis of sequencing data

Sequencing data are transferred to a platform for secure storage and analysis of sensitive research-related data at the University of Oslo [54]. The analysis of metagenomic sequencing data is handled in a uniform manner using a customizable workflow manager [55]. To establish a quality-filtered dataset, standard filters are applied: sequences corresponding to adapters used in library preparation, being of low quality [56] and those mapping to the human genome [57], with subsequent quality control of filtered sequencing reads [58].

Taxonomic classification and determination of microbial gene content, including functional annotation (e.g. using gene ontology and KEGG databases) will be performed using publicly available tools. Abundance measures will be used to calculate taxonomic and functional alpha and beta diversity, as well as serving as input for machine learning approaches aimed at producing classifiers for high-risk individuals in a data-driven manner. Further metagenome-derived measures may include identification of metagenome-assembled genomes, strain-level analysis and description of the gut virome.

#### Questionnaires

Two questionnaires are used to collect data on diet, lifestyle and demographic information; a food frequency questionnaire (FFQ) and a general lifestyle and demographics questionnaire (LDQ). Self-reported dates of questionnaire completion are registered in the project database. Returned questionnaires are reviewed manually before scanning and further processing. In cases of low-quality data, participants are contacted for clarification.

##### Assessment of dietary intake

Dietary intake is assessed using a semiquantitative, 14-page FFQ, designed to assess the habitual diet during the preceding year. The questionnaire is a modified version of an FFQ developed and validated by the Department of Nutrition, University of Oslo [59–64]. The questionnaire has been validated for both energy intake [59–61], intake of macro and micronutrients [59, 61, 64], as well as selected food items and groups [61–64]. The questionnaire includes 23 main questions, covering a total of 256 food items, as well as a free-text field for entries of food items not covered by the questionnaire. For each food item (except one on preferred types of fat for cooking), participants are asked to record frequency of consumption, ranging from never/seldom to several times a day, and/or amount, typically as portion size given in various household units (e.g. deciliters, glasses, cups, spoons). In total, there are 249 questions on frequency, 204 on portion size, one on preferences and nine other, mostly related to meal patterns (Additional file 1**, supplementary Table 1**).

As with any dietary assessment method, the FFQ is prone to errors due to inaccurate reporting and missing answers. Therefore, to mitigate such errors, a standardized framework for how to review and evaluate FFQ quality has been developed. A detailed overview of the framework is given in Additinoal file 2**, supplementary Fig. 1**. In brief, incoming FFQs are reviewed by trained personnel according to a set of predefined criteria. Scanning of questionnaires is performed using the Cardiff TeleForm program (Datascan, Oslo, Norway). The dietary calculation system KBS (short for “**K**ost**b**eregnings**s**ystem”), developed at the Department of Nutrition, University of Oslo, is used to calculate food and nutrient intake. The latest version of the food database (i.e. AE-18 or newer) will be used, which is largely based on the Norwegian Food Composition Table [65]. In line with common practice in nutrition studies, missing answers are imputed as zero intake [61, 63, 66, 67] and observations with extreme energy intake levels in both the upper and lower range will be excluded [68].

The main focus of the dietary analyses will be on foods and drinks linked to the risk of CRC and its precursor lesions, including intakes of alcohol, red and processed meat, wholegrains, foods containing dietary fiber, dairy products and calcium supplements [69]. Dietary intake will also be studied holistically by employing various dietary indices such as the 2018 World Cancer Research Fund/American Institute for Cancer Research (WCRF/AICR) index for adherence to cancer prevention recommendations [70].

##### Assessment of lifestyle and demographic data

Lifestyle and demographic data are assessed using a four page questionnaire based on questions used in previous national surveys [71, 72]. Prior to the study start, the questionnaire was piloted in a targeted population and adjusted based on feedback from pilot study participants. The questionnaire has ten main questions covering demographic factors (national background, education, occupation and marital status), diagnosis of CRC among first-degree relatives, presence of chronic bowel disorders and food intolerances, removal of the appendix, mode of delivery at birth, smoking and snus (i.e. smokeless tobacco) habits, recent use of medications, the past years’ physical activity level and use of regular and cultured milk, which is not completely covered in the FFQ (see Table 3 for a detailed overview). In the questions concerning smoking and snus habits, participants are asked to recall their current habits, including the daily number of cigarettes/snus portions, as well as years since possible cessation and total years of use. Questionnaires are scanned and processed using the Cardiff TeleForm program (InfoShare, Oslo, Norway).

### Registry data

Data collected in the CRCbiome study will be linked to national registries, including the Norwegian Prescription Database and the Cancer Registry of Norway, using personal identification numbers. Complete data linkages will be undertaken twice during active follow-up: after all participants have completed baseline and diagnostic information from follow-up colonoscopies is available, and then after the one-year follow-up is completed. In addition, linkage to the Cancer Registry of Norway will be performed at least once during the 10 year follow-up period.

#### Norwegian prescription database

The Norwegian Prescription Database [73] will be used to obtain information on medication history prior to CRC screening, and during the first year of follow-up. The registry contains data on all medications prescribed to Norwegian citizens since 2004. Prescription drugs are categorized according to the Anatomical Therapeutic Chemical (ATC) system, a hierarchical classification system developed by the WHO [74, 75]. For each drug, the number of packages dispensed, the number of defined daily doses (DDD), the prescription category, and the date of dispensing are registered.

Linkage to the Norwegian Prescription Database enables an in-depth analysis of associations between drug use, the gut microbiome and advanced colorectal lesions. Initially, we will perform drug-wide association analyses to screen for potential associations, adjusting for key covariates. Detected associations will then be examined in detail, including a more refined categorization of drug variables, robust covariate adjustments as well as the analysis of timing and dose-response relations. Prescription histories will also be used as a proxy for life-long burden of chronic diseases. To examine the representativeness of the drug profiles discoverd in the CRCbiome study, a randomly selected control group drawn from the National Population Registry, might be included.

#### Cancer registry of Norway

Information on clinicopathological characteristics, cancer therapy, as well as outcomes assessed as part of passive follow-up, will be obtained from the Cancer Registry of Norway [76]. The Cancer Registry of Norway has recorded incident cancer cases on a nationwide basis since 1953 and has been shown to have accurate and almost complete ascertainment of cases (98.8% for the registration period 2001–2005) [77]. According to recent estimates, about 93% of all cancer cases and ≥ 95% of cancers in the colon and rectum are morphologically verified [48]. Cancer diagnoses are recorded using the International Classification of Diseases, version 10 (ICD-10). Mortality data in the registry are obtained from the Cause of Death Registry and coded using the same ICD-10 categories as for the incidence data.

### Data processing and management

To facilitate project administration, including recruitment and follow-up of participants, custom software has been developed. This application communicates with two project specific databases (i.e. the BCSN and CRCbiome databases). Only authorized data manager personnel have complete access to the datasets. A simplified version of the data generation process is depicted in Fig. 2.

**Fig. 2 Fig2:**
[figure not shown]
Simplified version of the data generation process in CRCbiome. The figure is created based on free images from Servier Medical Art (Creative Commons Attribution Liscence, creativecommons.org/liscences/by/3.0/) and Stockio (https://www.stockio.com/)

In line with common practice for linkage with national registries [78], linked data will receive unique ID numbers specific to the particular project. Linkage of research data will be performed by the data controller. For the metagenome data, which due to its size cannot be transferred using ordinary methods, linkage will be performed in-house by an independent data manager without access to other parts of the data than those strictly necessary for linkage.

All data collected in the CRCbiome study will be stored and analyzed at a platform for secure handling of sensitive research-related data, operated by the University of Oslo [54]. Access to research data for external investigators, or use outside of the current protocol, will require approval from the Norwegian Regional Committee for Medical and Health Research Ethics and a data access committee (information available on the project web site [79]). Research data are not openly available because of the principles and conditions set out in articles 6 [1] (e) and 9 [2] (j) of the General Data Protection Regulation (GDPR).

### Statistical analyses and sample size considerations

The number of participants to include was chosen with the aim of providing adequate power for the development of a highly sensitive classification algorithm via data-driven analyses of gut metagenomes that will accurately identify FIT-positive individuals in need of clinical intervention.

The classifier will be trained using counts of taxonomic units, signature and genes categorized according to gene ontology or pathway membership from metagenomes, FFQ, demographic and lifestyle data as input variables, and advanced colorectal lesions as outcome (i.e. group group 3 and group 4, Table 2). The CRC risk classification will be done using machine learning algorithms suited to metagenome data, such as lasso regression [80], support-vector machines [81], random forests [82], multi-layer perception neural networks [83] and scalable tree boosting [84] algorithms. Evaluation of the classifier will be conducted in a leave-out test set. As outlined below, we believe that with sufficient sample size, development of a classifier with a sensitivity of 0.95 is achievable in the training set, being within the range of published reports [30, 33].

Interpretation of the classifier will be sought by post hoc analysis, quantifing the importance of individual features (taxa, genes and pathways) in making predictions. Stratified analyses will be done to evaluate the classifier within different subgroups of the population (e.g. by age group, sex and screening center).

With a projected classifier sensitivity of 0.95 and a minimally acceptable sensitivity of 0.8, at 80% power and 95% confidence level, 50 participants with advanced colorectal lesions are required in the test set [85]. Classifier specificity in the setting of FIT-positive individuals will have a lower requirement, and we therefore set the expected classifier specificity to 0.75 and a minimally acceptable specificity of 0.6, thus requiring 100 participants with normal findings in the test set. Based on initial recruitment, we expect a participation rate of 58%, with 26% of participants having findings of advanced lesions or CRC (Table 2). By inviting 2700 FIT-positive BCSN participants, and splitting the training and test sets 80/20, a projected number of 1253 and 313 participants will constitute the training and test sets, respectively, which will include adequate numbers of participants with both advanced colorectal lesions and normal findings in the test set. With this sample size, we will also be able to perform stratified analyses. The machine learning analyses will be complemented by various multivariate regression analyses, stratified by the covariates outlined above.

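### A single 80/20 split is the only stated out-of-sample estimate of accuracy, so intervals are nominally about 2.2 times as wide as whole-cohort cross-validation would give, most harmfully in the promised subgroup evaluations

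*Protocol article*

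**What the plan says.** All of this is in the Protocol article, section Statistical analyses and sample size considerations, unless noted.

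- **Evaluation:** "Evaluation of the classifier will be conducted in a leave-out test set".
- **Split:** "splitting the training and test sets 80/20, a projected number of 1253 and 313 participants will constitute the training and test sets, respectively".
- **Sizing for sensitivity:** "With a projected classifier sensitivity of 0.95 and a minimally acceptable sensitivity of 0.8, at 80% power and 95% confidence level", from which "50 participants with advanced colorectal lesions are required in the test set".
- **Sizing for specificity:** "we therefore set the expected classifier specificity to 0.75 and a minimally acceptable specificity of 0.6", with 100 participants with normal findings required in the test set.
- **Candidate methods:** given as examples, "such as lasso regression [80], support-vector machines [81], random forests [82], multi-layer perception neural networks [83] and scalable tree boosting [84] algorithms".
- **Subgroups:** the classifier is to be evaluated by, for example, age group, sex and screening center, and the sample size is said to permit stratified analyses.

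The Discussion projects about 409 participants (26%) with advanced lesions or CRC. The article names no cross-validation or other resampling, and no step by which algorithm, feature set and cut-off are settled before the test set is used.

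**The concern.** Developing the classifier is the primary aim, so its sensitivity and specificity are the headline results. Under the stated design they come from one random fifth of the cohort. The other four fifths train the model and add nothing to the accuracy estimate, although cross-validation over the same cohort could give every participant an out-of-sample prediction.

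For one overall comparison with the 0.80 minimum, a fifth may be enough. For the stratified evaluation it is thin. A stratum holding half the cohort would have about 41 test-set lesions, fewer than the 50 that the article requires for its overall comparison. A real difference between the sexes or between centers could not be told from chance, and the figures would also depend on which split happened to be drawn.

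**Working it through.** **Inputs.** 2700 invited, 58% participation and an 80/20 split (sample-size section). Groups 3 and 4 make up 4.4 + 18.1 + 3.6 = 26.1% and Group 1 makes up 11.2 + 2.4 + 18.2 = 31.8% (Table 2). About 409 lesions are projected (Discussion).

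**1. Reproduce the plan's figures.**
- 2700 × 0.58 = 1566. Then 1566 × 0.8 = 1252.8 and 1566 × 0.2 = 313.2, matching 1253 and 313.
- Lesions: 1566 × 0.261 = 409 overall and 313 × 0.261 = 82 in the test set, leaving 409 − 82 = 327 in training.
- Group 1: 1566 × 0.318 = 498 overall and 313 × 0.318 = 99.5 in the test set.
- Required lesions, 0.80 against 0.95, two-sided 5%, 80% power: 42 by the score formula, 49 with continuity correction, 48 by exact binomial. The stated 50 agrees with the last two to within 2.

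**2. Is the overall test adequate?** With 82 lesions the exact one-sided 2.5% rule is a pass at 73 or more: P(X ≥ 73 | 82, 0.80) = 0.023 and P(X ≥ 73 | 82, 0.95) = 0.99. With 81 lesions the power is 98%. Over random splits (taking 407 lesions, 26% of 1566) the test set would hold 68 to 95 lesions in 95% of draws. The test is adequate.

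**3. Precision.** Wilson 95% interval, with z = 1.96:

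(p + z²/2n ± z·√(p(1−p)/n + z²/4n²)) / (1 + z²/n)

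| Quantity | Leave-out set | All participants, out-of-fold |
|---|---|---|
| Sensitivity 0.95 | n = 82: 88-98% | n = 409: 92-97% |
| Sensitivity 0.80 | n = 82: 70-87% | n = 409: 76-84% |
| Specificity 0.60, Group 1 | n = 100: 50-69% | n = 498: 56-64% |
| Specificity 0.75, Group 1 | n = 100: 66-82% | n = 498: 71-79% |

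The nominal width ratio is √(1566/313) = √5 = 2.24. This treats out-of-fold predictions as independent. If dependence between folds inflates the cross-validated standard error by 12% (assumption) the ratio is 2.24/1.12 = 2.0; at 20% it is 2.24/1.20 = 1.86.

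**4. Subgroups.** Assume a stratum holding half the cohort: 82/2 = 41 test-set lesions and 409/2 ≈ 205 overall. At a sensitivity of 0.80 the intervals are 65-89% and 74-85%. CRC alone (3.6%) would give 313 × 0.036 ≈ 11 test-set cases.

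**5. Conditional check on selection.** Suppose, which the article does not say, that five candidates with true sensitivity 0.80 were all scored on the same 82 lesions and the best one reported. A Gaussian-copula simulation with per-person correlation 0.5 to 0.9 (assumed) gives an optimism of about 3 to 4 points. The chance of reaching 73/82 is about 7-10%, against 2.3% for one prespecified classifier.

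**The case against.** The strongest reply is that an untouched leave-out set is a legitimate choice. It protects against analyst reuse in a way that cross-validation does not, it estimates the performance of one frozen classifier, and it was sized by an explicit criterion that it meets comfortably. At the planned sensitivity of 0.95 the interval on 82 lesions lies clear of 0.80. All of this stands, and it is why the leave-out result should remain decisive. It also stands that 2.2 is an upper figure, because out-of-fold predictions come from overlapping fits and describe a modelling procedure rather than a single model. The reply does not cover the subgroup evaluation, which the sizing criterion never addressed.

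A reader might go further and infer that, with several algorithm families named and no selection step described, the choice must fall on the test set and the reported accuracy will be optimistic. The article does not support that. It speaks of one classifier, places its development in the training set and reserves the leave-out set for evaluation. Tuning within the 1253 fits this wording, and a condensed article may leave it to the full protocol or analysis plan. The algorithms are introduced as examples, so five is not a fixed candidate count. The best-of-five figures also assume models lying exactly at the failing bound. At a true 0.95 the optimism would be about 0.9 to 2.8 points (correlation 0.9 to 0).

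**Conclusion.** The concern holds as one of efficiency. The plan is neither underpowered overall nor shown to be biased. One split is the only stated out-of-sample estimate, and it uses about 82 of 409 lesions. Overall intervals are nominally about 2.2 times as wide as whole-cohort cross-validation would give, or about 1.9 under an assumed 20% inflation of the standard error. The practical loss is in the stratified evaluation, where a half-cohort stratum would carry a 95% interval about 24 points wide at a sensitivity of 0.80, against about 11 points. These figures rest on the projected enrolment and Table 2 percentages, on Wilson intervals and, for subgroups, on an assumed even division. Optimism from choosing the best of several candidates is a conditional risk that one sentence would close. The change is worth making but is not essential to the validity of the primary comparison.

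**What to change.** Keep the 80/20 split and the leave-out result as the one that decides against the 0.80 and 0.60 minimums. Add to Statistical analyses and sample size considerations:

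1. *After the leave-out result is fixed, the full modelling procedure, including selection of algorithm, features and cut-off, will be run unchanged as repeated nested cross-validation over all participants. Out-of-fold sensitivity and specificity will be reported beside the leave-out result, overall and by age group, sex and screening center, with bootstrap intervals.*
2. As a clarification: *algorithm, features and cut-off will be chosen by resampling within the training participants only. One classifier will then be locked and the test set opened once.*

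The cost is computing time and a few sentences, with no new participants or samples. The cross-validated figure describes the modelling procedure, not the frozen classifier, and should be labelled so. The interval that decides the primary comparison stays as wide as now; the gain is in the supporting overall estimate and in the subgroups.

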### Participants and eligibility

The BCSN trial includes 139,291 women and men aged 50–74 years in 2012, living in South-East Norway. Of these, 70,096 have been randomized to FIT screening. So far, the cumulative participation rate for the first three FIT rounds has been 68% [46]. All screening participants with a positive FIT test are eligible for the CRCbiome study. Recruitment for the CRCbiome study started in 2017, and will continue until a minimum of 2700 participants have been invited. So far, 2426 have been invited and 1413 (58%) have agreed to participate. With the current participation rate, we expect recruitment to be completed by March 2021 with a final number of participants of about 1600 (see below for the sample size considerations). Recruitment bias will be evaluated by comparing key characteristics of the included participants, such as age, sex and BMI, with those of the BCSN.

The main inclusion and exclusion criteria for the BCSN trial and the CRCbiome study are listed in Table 1.

**Table 1 Tab1:** Inclusion and exclusion criteria in the BCSN trial and CRCbiome study

Inclusion criteria	
*BCSN*	Aged 50–74 years old in 2012
	Resident in selected municipalities in South-East Norway (Østfold, parts of Akershus and parts of Buskerud)
*CRCbiome*	FIT positive test (i.e. hemoglobin > 15 mcg/g feces) and invited to a follow-up colonoscopy

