**Exclusion criteria**	
*BCSN*^a^	Death
	Moving out of the area
	Reaching the upper age limit
	Diagnosed with CRC
*CRCbiome*	Not attending screening colonoscopy
	Low DNA concentration
	Low sequencing yield (< 2 gigabases)

^*a*^*Exclusion criteria apply for individuals who died, moved out of the area, reached the upper age limit, or were diagnosed with CRC before they were due for invitation*

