### Outcome variables

For the first two aims, the outcome variable will be defined based on the colonoscopy result. Participants will be grouped into four main categories: no confirmed neoplastic findings (Group 1); non-advanced lesions (Group 2); advanced lesions (Group 3); and CRC (Group 4) (Table 2). The advanced lesions group consists of both advanced adenomas (any adenoma with villous histology, high-grade dysplasia or polyp size greater than or equal to 10 mm) and advanced serrated lesions (any serrated lesion with size ≥10 mm or dysplasia). In addition to separating by stage of the carcinogenic process, we may further subdivide lesions by clinicopathological features, including histopathological subtype (e.g. adenomas versus serrated lesions) and site of occurrence (proximal versus distal colon). Also of interest is the potential for distinct roles of environmental factors and the gut microbiome in the two main pathways of colorectal carcinogenesis: the adenoma-carcinoma pathway, and the serrated carcinoma pathway.

**Table 2 Tab2:** Main outcomes of the screening colonoscopy among CRCbiome participants with preliminary distribution in percentages as of November 2020

Colonoscopy result	Percentages^a^
FIT+, no colonoscopy	3.6

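### The projected 1253/313 training and test sets count consenting participants, with no deduction for the protocol's own exclusions, and leave no reserve for technical loss against the 100 normal findings required

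*Protocol article*

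**What the plan says.** All references are to the protocol article.

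- **Statistical analyses and sample size considerations.** The projection runs from invitations to set sizes in one step: "By inviting 2700 FIT-positive BCSN participants, and splitting the training and test sets 80/20" is said to yield the result that "a projected number of 1253 and 313 participants will constitute the training and test sets, respectively, which will include adequate numbers of participants" of both kinds. The test set needs 50 participants with advanced lesions (sensitivity 0.95 expected, 0.8 minimum) and 100 with normal findings (specificity 0.75 expected, 0.6 minimum), at 80% power and 95% confidence. Both numbers are said to be met. The classifier's positive class is Groups 3 and 4.
- **Participants and eligibility.** The 58% comes from recruitment to date: "So far, 2426 have been invited and 1413 (58%) have agreed to participate". The 2700 is a minimum, and the expected final number is about 1600.
- **Table 1.** The CRCbiome exclusions include "Not attending screening colonoscopy", low DNA concentration, and sequencing yield below 2 gigabases.
- **Table 2 (Outcome variables).** The distribution is given for CRCbiome participants, and its first row is "FIT+, no colonoscopy" at 3.6%. Group 1, in which no neoplasia was confirmed, has three rows: 11.2%, 2.4% and 18.2%.

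**The concern.** A training or test set can contain only people who have an outcome label and usable sequence data. The projection treats everyone who consents as such a person, although the same article lists three reasons for removing participants and gives a figure for one of them. The stated sizes are therefore too large.

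The size of the test set also supports the claim that both case counts are met. That claim has a wide margin for advanced lesions. For normal findings, a term the article does not tie to any of its four groups, it depends on which participants are counted, and under the Group 1 reading the expected count sits on the requirement itself. At stake are the accuracy of the stated sample size and whether a reader can verify the specificity claim.

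**Working it through.** **1. Reproducing the stated sizes.** 2700 × 0.58 = 1566. Then 1566 × 0.80 = 1252.8 and 1566 × 0.20 = 313.2, the printed 1253 and 313. No deduction enters. The Discussion's figure of about 409 advanced cases confirms the base: Groups 3 and 4 are 4.4 + 18.1 + 3.6 = 26.1%, and 1566 × 0.261 = 408.7.

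**2. Table 2's denominator.** No colonoscopy 3.6, Group 1 31.8, Group 2 (6.4 + 23.6 + 8.4) 38.4, Groups 3 and 4 26.1. The sum is 99.9, so the table reaches 100%, up to rounding, only with the no-colonoscopy row included.

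**3. Removing those without colonoscopy.** 1566 × 0.036 = 56 people, about 11 of them in the test set (313.2 × 0.036 = 11.3). Remaining: 1566 × 0.964 = 1509.6, split 1207.7 / 301.9. With the unrounded consent rate, 2700 × 1413/2426 = 1572.6 and 1572.6 × 0.964 = 1516.0. With 1600 participants, 1600 × 0.964 = 1542.4. Each is below 1566.

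**4. Expected test-set counts before technical loss.**

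| Category | Share | Count in 313.2 | Required |
|---|---|---|---|
| Groups 3 and 4 | 26.1% | 81.7 | 50 |
| Group 1 | 31.8% | 99.6 | 100 |
| Groups 1 and 2 | 70.2% | 219.9 | 100 |

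Removing the no-colonoscopy participants does not change these counts, because they are already in the denominator: 301.9 × 31.8/96.4 = 99.6. (Applying 31.8% to 301.9 would deduct them twice.)

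Group 1 under the article's other inputs: 1572.6 × 0.2 × 0.318 = 100.0 at the unrounded rate, and 1600 × 0.2 × 0.318 = 101.8.

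**5. Technical loss.** The article gives no rate for low DNA or low yield. The rates below are assumptions, applied equally to all groups.

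| Assumed loss | Analysable (train/test) | Group 1 | Groups 3 and 4 | Groups 1 and 2 |
|---|---|---|---|---|
| 0% | 1510 (1208/302) | 99.6 | 81.7 | 219.9 |
| 5% | 1434 (1147/287) | 94.6 | 77.7 | 208.9 |
| 10% | 1359 (1087/272) | 89.6 | 73.6 | 197.9 |

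Starting from 1600 participants, the margin over 100 disappears at a loss of 1 − 100/101.76 = 1.7%.

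**6. Power for specificity.** Exact one-sample binomial test, 0.75 against 0.60, one-sided 0.025 (the article does not state sidedness): 0.896 at n = 100, 0.869 at n = 95, 0.835 at n = 90 and 0.794 at n = 85. An expected count of about 85 corresponds to a loss of 15% (99.6 × 0.85 = 84.7). At one-sided 0.05, power at n = 85 is 0.904.

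**The case against.** The strongest reply is that nothing important is lost. The pre-loss gap of 0.4 of a participant comes from rounding 58.24% to 58%; on the unrounded rate or with 1600 participants the expectation reaches 100. The one exclusion the article quantifies leaves both test-set counts unchanged. The planned power is 80%, and 90 to 95 Group 1 participants still exceed it. If specificity is assessed in everyone outside the positive class, about 220 are available. All of this stands, and it limits the point to a restatement of size and an absent reserve.

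It does not rescue the stated sizes. Participants without colonoscopy have no outcome and are excluded by Table 1, so they cannot belong to either set, however normal findings is read.

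A reader might infer four stronger things, none of which the document supports:

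- **The test set already falls short of 100.** This rests on the rounded participation rate alone.
- **Only 35 normal participants will be available**, from 11.2% of 313, with exact power of 0.32. This takes normal findings to mean only the Negative row, one of three within Group 1. The article's analysis categories are Groups 1 to 4, so this is the least likely reading.
- **The chance of reaching 100 is only about one half.** This assumes a simple random split. The article does not say how the split is drawn, and that detail may be left to an analysis plan.
- **People who returned one questionnaire are also lost.** Table 1 does not exclude them, no rate is given, and handling of missing inputs may likewise be set out elsewhere.

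**Conclusion.** The point holds as an overstated sample size. On the article's own 2700 and 58%, the sets can hold at most about 1510 analysable participants (1208/302) rather than 1566 (1253/313), a reduction of 3.6% before any technical failure. This needs no outside assumption beyond the preliminary Table 2 percentages continuing to apply.

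The second part depends on reading normal findings as Group 1. Then the expected count is 99.6 to 101.8 against 100, with no reserve for the DNA and sequencing failures that the article itself names. The further counts of about 90 to 95 rest on an assumed loss of 5 to 10%. Even there, power for specificity stays above the planned 80%, so the weakness lies in the stated figure and its missing margin, not in a demonstrated loss of power. The sensitivity requirement is met with room to spare under every rate shown.

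**What to change.** 1. Restate the training and test sizes as analysable participants after the Table 1 exclusions: about 1510 (1208/302) before technical loss, then reduced by a stated DNA and sequencing failure rate, taken from samples already processed if that is known.
2. Give the expected test-set count for each diagnostic group on that basis.
3. Name the specificity denominator. Either use Group 1, with about 90 to 100 expected and the power that gives, or use all participants outside Groups 3 and 4 (Groups 1 and 2, about 200 to 220). The second matches the classifier outcome in the same section and meets the requirement of 100.

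The cost is a few revised figures and one definition. No additional recruitment is needed.
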